#### Eating Behaviors

This is related to secondary objective 5. Eating behaviors will be assessed using the following four subscales from the Children’s Eating Behavior Questionnaire (CEBQ) [69]: “satiety responsiveness” (eating appropriately in response to appetite), “food responsiveness,” “food enjoyment” (eating in response to environmental food cues rather than hunger), and “slowness in eating.” Although a Baby Eating Behavior Questionnaire has been developed [70], it is designed for infants who are exclusively milk fed, so it would not capture complementary feeding. Food fussiness will be measured using five items in the “picky eating” subscale of the Toddler-Parent Mealtime Behavior Questionnaire [71]. We have demonstrated the internal consistency and reliability of these scales in New Zealand infants at 12 months of age, with Cronbach α ranging from .83 to .90 [58]. Participants will also be asked whether they feed their infants any foods of particular cultural relevance. Feeding behaviors will be determined by observing how infants eat and how parents react in response to hunger and satiety cues by videotaping one evening meal (at which solid foods are offered) in each infant recruited in the Dunedin cohort (n is approximately 300). Participants will be issued a GoPro wide-angle video camera (Hero 2018; GoPro Inc) and tripod at their first appointment and asked to video record the main meal on the day for which the second 24-hour recall will be obtained. The camera will take a continuous video from approximately 10 minutes before the infant first joins the meal to when they leave it. Videos will be coded using the Responsiveness to Child Feeding Cues Scale [72].

#### Dental Health

This is related to secondary objective 6. Photographs of the infant’s upper and lower teeth will be taken by trained interviewers using a dedicated study Oppo Reno2 Z (Oppo) mobile phone with a small portable Smile Light MDP lighting source specifically designed for taking dental pictures [73]. These images will be examined by a single registered dental practitioner, with blinded evaluation of a subset by another examiner, using validated indices for caries and developmental defects of enamel, which have a positive correlation with dental caries [74].

#### Oral Motor Skill Development

This is related to secondary objective 7. The questionnaires administered at the final appointment include the validated Child Oral Motor Proficiency Scale (ChOMPS) to identify oral motor and eating skill delay [75,76] and the Pediatric Eating Assessment Tool (PediEAT) to measure behaviors that characterize symptoms of feeding difficulties [77,78]. Both questionnaires have age-based reference values for infants and rely on parent reporting [79,80].

#### Choking

This is related to secondary objective 8. The questionnaire administered at the initial appointment will include questions on choking since birth. We developed these retrospective questions for previous work in this age group and have demonstrated that they provide data that are comparable to choking data collected prospectively using a daily choking calendar [81].

### Statistical Analysis

We expect that there will be crossover between BLW/TSF status and pouch use. We will be able to explore whether mean differences in energy and nutrient intake, as well as other measures, between pouch users and nonusers are different for those who use BLW and those who do not. These results will be stratified by BLW/TSF status, and estimated differences will be compared.

Regression models will be used to determine differences between groups. Propensity score matching will be undertaken to reduce the bias caused by differences in demographics between the groups (eg, maternal education and ethnicity), infant age (to the nearest week), and sex. Propensity score matching is not like traditional paired matching, where each individual is matched to another individual in the other group according to covariates. Instead, propensity score matching uses a participant’s propensity score (found using covariates) and estimates what their outcome (eg, energy intake) would have been if they were in the other of two dichotomous groups. By using this method, we expect the estimates will more closely represent a potential causal effect [53]. Another advantage is that it allows data from the whole sample to be used, unlike a traditional matched analysis in which only matched pairs are analyzed.

Estimates of BLW, frequent pouch use, nutrient intake, status, and adequacy will be calculated for the whole sample along with 95% CIs. If the sample is not demographically representative of the wider population, statistical weighting of these estimates will be undertaken using the survey command in Stata (StataCorp).

Nutrient intake will be determined using 24-hour recall data adjusted to provide estimates of usual intake (using the MSM method [65]). Adequacy of intake will be determined as follows: for zinc (for which an estimated average requirement [EAR] is available for New Zealand and Australia [82]), the EAR cut point method will be used; for iron (for which an EAR and tables of probabilities of inadequate intakes are available for the United States of America and Canada [83]), the full probability approach will be used [83]; for other nutrients (only an adequate intake [AI] is available for this age group in New Zealand and Australia [82]), mean group intake above the AI will be considered to indicate adequacy, but a conclusion as to inadequacy will not be possible if mean group intake is below the AI [84]. The BRINDA method [60] will be used to adjust plasma ferritin, and therefore, body iron and iron status, for the impact of inflammation.

The best-fitting polynomials to predict breast milk intake will be estimated by regression models using fractional polynomial functions of variables, such as age, sex, body weight, and food and beverage intake (eg, kJ/day). This will result in equations that can be used to predict breast milk intake based on a variety of input variables. Ideally one based on data that can be collected in a single clinical appointment, and another that uses data requiring more extensive collection in a research or surveillance setting.

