### Participants and Recruitment

In total, 625 parents/guardians who have an infant less than 9.9 months of age will be recruited from two regions of New Zealand (Dunedin and Auckland) to participate in the study when their infant is aged 7.0 to 9.9 months. Recruitment will occur by advertisement and word of mouth and will target all infants rather than those adopting BLW, TSF, or food pouch use. We aim to recruit a sample that is broadly representative of the ethnicity and socioeconomic status of New Zealand children. It is not feasible to recruit a truly representative sample using typical methods, such as electoral roll and door knocking, because they would identify very few infants in the narrow age band that is necessary for this study (because diet changes so rapidly in infancy). We will, however, collect data from a diverse range of ethnic and socioeconomic groups by (1) engaging with Māori and Pasifika community health organizations to assist with recruitment, (2) targeting recruitment in suburbs with a high proportion of Māori, Pasifika, and Asian populations, and (3) having research team members who have experience working with or who culturally identify with Māori, Pasifika, and Asian communities. We will also statistically weight the estimates to account for demographic disparities if appropriate. The study has ethical approval from the Health and Disability Ethics Committees New Zealand (19/STH/151), and written informed consent will be obtained at the first appointment. The study is registered with the Australian New Zealand Clinical Trials Registry (registration number: ACTRN12620000459921).

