#### Infant Diet

This is related to secondary objective 1. Information on infant nutrient intake and adequacy, food group intake, dietary patterns, and culturally important foods will be obtained using interviewer-administered multiple pass 24-hour recalls collected at the first and second appointments. The two 24-hour recalls take place on different days of the week to capture variation in intake between days. Collecting two 24-hour recalls will enable us to calculate “usual intake” using the multiple source method (MSM) for estimating usual dietary intake of individuals [65]. Photograph prompts will be used to assist recall of foods eaten. Participants will be asked to photograph (using their own smartphone or a camera provided) the eating surface (eg, plate, high chair surface, and table) at the start of all meals and snacks from midnight to midnight on the day before the appointment. The quality of the photographs will not be important as long as they are clear enough to remind the parent what the child ate. Diet recalls will be analyzed with FoodWorks (version 10, Xyris Software) using the New Zealand Food Composition database FOODfiles 2018 Version 01 [66]. Nutrient information for commercial infant foods and milk will be determined by generating recipes using the ingredients lists on food products modified to match the nutrient information panel on the packet so that the contribution of nutrients that do not appear on the nutrient information panel can be included [15]. Information on supplement use will be collected by a questionnaire.

Particular focus will be on free sugars and added sugars given a recent small study [45] suggested that even by 7 months of age, 12% of New Zealand infants may already be consuming free sugars at levels that are above the WHO recommendation [67]. Parents are discouraged from adding sugar to infants’ diets because it is unnecessary and may increase liking of sweet foods [2]. In addition, the WHO recommends that free sugars should be <5% of energy intake due to the dose-response relationship between free sugar intake and dental caries (even in populations with water fluoridation) [67]. Data on free sugars and added sugars are available in the New Zealand food composition database [66,68].

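### Ordinary or survey-command 95% CIs computed directly on MSM usual intakes would be too narrow for mean intake and for EAR cut-point adequacy, and the plan does not say how those CIs will be obtained

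*Protocol article*

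**What the plan says.** Three statements in the Protocol article have to be read together.

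- **The variable.** Statistical Analysis: "Nutrient intake will be determined using 24-hour recall data adjusted to provide estimates of usual intake (using the MSM method". Infant Diet: "Collecting two 24-hour recalls will enable us to calculate “usual intake” using the multiple source method (MSM) for estimating usual dietary intake of individuals". Each infant therefore has one adjusted value, built from two recalls. The same section recognises day-to-day variation: "The two 24-hour recalls take place on different days of the week to capture variation in intake between days". Its size is not given.
- **The promise.** Statistical Analysis: "Estimates of BLW, frequent pouch use, nutrient intake, status, and adequacy will be calculated for the whole sample along with 95% CIs". Adequacy is judged by the EAR cut point for zinc, by the full probability approach for iron, and for other nutrients by comparing mean intake with the AI.
- **The tool.** If the sample is not demographically representative, "statistical weighting of these estimates will be undertaken using the survey command in Stata". Participants and Recruitment says that a truly representative sample is not feasible, so the weighted route is a realistic one.

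The article does not say how a standard error for an MSM-based mean or prevalence is obtained.

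**The concern.** A usual-intake adjustment exists to take day-to-day variation out of the individual values. That suits a description of the intake distribution. It does not suit the standard error of a sample mean, because each infant was still observed on only two days and the within-infant noise of those days remains in the sampling error. An ordinary or survey standard error treats the adjusted values as observed data. It sees the reduced spread and so understates the error. It also ignores that the variance components behind the adjustment were themselves estimated. Survey replicate weights do not cure this unless the MSM step is rerun in each replicate.

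Secondary objective 1 is to estimate nutrient intake and adequacy in New Zealand infants, and the Introduction says that comparable national data do not exist. The error bars on these figures would be quoted as they stand. They would be most overstated for nutrients with large day-to-day variation.

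**Working it through.** **The plan's own figure.** The only whole-sample precision stated for a prevalence is at least ±4% for frequent pouch use (Sample Size). With n = 625 the half-width at p = 0.5 is 1.96 × √(0.25/625) = 3.92 percentage points, so the figure reproduces. It involves no usual-intake step and is not in question. No width is stated for nutrient intake or adequacy.

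**Inputs**

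- From the documents: n = 625 (Participants and Recruitment), two recalls per infant (Infant Diet), nominal level 95% (Statistical Analysis).
- Assumed: λ = Vw/Vb, the within-infant to between-infant variance ratio, from 0.5 to 3; adjusted values whose variance equals Vb; normally distributed intakes; intake taken wholly from the recalls.

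**Mean intake**

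- Correct standard error: √((Vb + Vw/2)/n).
- Standard error computed on the adjusted values: √(Vb/n).
- Ratio of the second to the first: 1/√(1 + λ/2).
- Coverage: 2Φ(1.96 × ratio) − 1.

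Example for λ = 1: the ratio is 1/√1.5 = 0.816, 1.96 × 0.816 = 1.60, and coverage is 89.0%.

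The simulation used n = 625 and 5,000 runs. Each infant's two-day mean was shrunk towards the overall mean by a factor estimated from the sample, so that the adjusted values kept the estimated between-infant variance.

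| λ | SE ratio | Coverage by formula | Coverage simulated | Simulated, unadjusted two-day means |
|---|---|---|---|---|
| 0.5 | 0.894 | 92.0% | 92.6% | 95.2% |
| 1 | 0.816 | 89.0% | 89.0% | 95.3% |
| 2 | 0.707 | 83.4% | 83.3% | 95.5% |
| 3 | 0.632 | 78.5% | 77.4% | 94.7% |

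Outside this range the formula gives 93.5% at λ = 0.25 and 74.2% at λ = 4.

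**EAR cut-point prevalence.** In the same simulation, the share of adjusted values below a cut point was given the ordinary binomial interval, p ± 1.96 × √(p(1 − p)/n). Coverage by true prevalence:

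| λ | 5% | 10% | 20% | 30% | 50% |
|---|---|---|---|---|---|
| 0.5 | 90.8% | 91.4% | 92.4% | 93.3% | 92.7% |
| 1 | 86.5% | 87.2% | 88.4% | 90.0% | 91.1% |
| 2 | 77.4% | 77.9% | 80.1% | 84.3% | 86.8% |
| 3 | 68.1% | 68.3% | 73.0% | 78.6% | 83.1% |

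**Absolute size at λ = 1.** For a mean, the half-width on the adjusted values is 1.96/√625 = 0.078 between-infant SD. The correct one is 0.078 × √1.5 = 0.096. For a 20% prevalence, the binomial half-width is 1.96 × √(0.16/625) = 3.1 points. Coverage of 88.4% corresponds to a z of about 1.57, so the half-width needed is about 3.1 × 1.96/1.57 = 3.9 points.

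**Sensitivity to the form of shrinkage.** If the adjusted values were best linear predictions, the standard-error ratio for the mean would be 1/(1 + λ/2). Coverage would then be 88.3%, 80.9%, 67.3% and 56.7% at λ = 0.5, 1, 2 and 3. The direction is the same and the shortfall larger.

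**The case against.** The strongest reply is that the article states no CI formula. Bootstrapping infants through the MSM step would fit every sentence of it. The survey command is named only for conditional weighting, and a condensed article may leave the variance method to the full plan. All of this is correct. A reader might infer that the study's intervals will certainly be too narrow. The documents do not support that, and the point holds only for CIs computed directly on the adjusted values.

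Other parts of the reply also stand:

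- The variance ratio, and the exact spread of MSM output, are assumptions. A reader might take one coverage range as a result for intake and adequacy alike, but the range for means does not carry over to prevalences.
- The full probability approach for iron was not modelled, so no coverage figure can be given for it.
- Infant milk supplies more than half of energy at 7 months (Introduction). Breast milk is measured by isotope in 150 dyads and predicted by equation for other participants (Breast Milk Intake). Total intake of breastfed infants is therefore not simply two independent recall days, and the coverage figures do not transfer to it directly.
- Adequacy by mean against AI is a rule that uses no CI.
- The absolute widening is modest at n = 625, and the primary outcomes (iron status and BMI z-score) are untouched.

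What does not stand is that this is only absent detail. The article names one intake variable, one estimation tool for weighted estimates, and a 95% level. Applied together as written, without an added variance step, they give standard errors that omit the within-infant variance.

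**Conclusion.** The point holds in conditional form. If the 95% CIs for whole-sample intake and EAR cut-point adequacy are ordinary or survey-command intervals on MSM values, they will under-cover. Under the stated assumptions (λ from 0.5 to 3, between-infant variance kept, normal recall-based intake), a nominal 95% CI covers about 92% falling to 78% for a mean. For an EAR cut-point prevalence it covers about 93% falling to 68%, with the lowest figures at low prevalence and high λ. Only the direction can be taken from the plan. The size rests on λ, which the documents do not give.

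The promise of 95% CIs also covers BLW, frequent pouch use and iron status. MSM plays no part in those, so their intervals are not affected. The mean intake itself is not biased by this. The point concerns the stated precision of a secondary objective and deserves correction before analysis, but it does not threaten the primary comparisons.

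**What to change.** Add a short statement to the analysis plan:

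- CIs for mean intake come from the unadjusted two-day mean per infant, survey-weighted if weighting is used. In the simulation this gave 94.7% to 95.5% coverage.
- CIs for usual-intake percentiles and for adequacy (EAR cut point and full probability) come from a bootstrap of infants. The usual-intake step is rerun in each resample, together with the breast-milk prediction and the weighting where these are used.
- The estimated within:between variance ratio is reported for each nutrient, so that readers can see how much the adjustment matters.

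No new data are needed. The cost is analyst and computing time, and the published intervals become somewhat wider.

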## Results

This observational study has full ethical approval from the Health and Disability Ethics Committees New Zealand (19/STH/151) and was funded in May 2019 by the Health Research Council (HRC) of New Zealand (grant 19/172). Data collection commenced in July 2020, and the first results are expected to be submitted for publication in 2022. Data collection will only take place while New Zealand is in Alert Levels 1 or 2 during the COVID-19 pandemic. The Otago and Auckland regions of New Zealand, where the data collection will take place, have been in Level 1 for all but 7 weeks in Otago (all at Level 2) and 11 weeks in Auckland (7 weeks at Level 2 and 4 weeks at Level 3) since July 2020, as overall case numbers in New Zealand remain extremely low (<2000 in a population of more than 5 million). As daily life is essentially normal in Level 1 with the exception of closed international borders and Level 2 just requires some physical distancing and appropriate hygiene recommendations, we feel confident that the pandemic will have relatively little effect on our data.

## Discussion

This large observational study will provide much needed data on nutrient intake (including breast milk intake) and nutritional status (specifically iron status, growth, and dental health) in a large diverse sample of New Zealand infants. However, our data will also have considerable international appeal given the lack of research assessing the implications for nutritional intake and health for those infants who obtain a large proportion of their food via baby food pouches. Similarly, determining how iron status, growth, nutrient intake, and choking risk may differ in infants following BLW compared with TSF is urgently warranted given the widespread interest in this alternative approach to complementary feeding worldwide.

## Appendix

Multimedia Appendix 1 Peer-reviewer reports and grant approval from Health Research Council of New Zealand.

Multimedia Appendix 2 Ethics approval.

## Abbreviations

AI: adequate intake
BLW: baby-led weaning
BRINDA: Biomarkers Reflecting Inflammation and Nutritional Determinants of Anemia
EAR: estimated average requirement
FFNZ: First Foods New Zealand study
FITS: US Feeding Infants and Toddlers Study
MSM: multiple source method
TSF: traditional spoon feeding
WHO: World Health Organization
